### Sample size

2.5

This study is an observational study designed to describe the LDL-C-lowering effectiveness and safety of LivaloZet^®^ Tablet in patients with dyslipidemia accompanied by metabolic syndrome. Rather than conducting formal hypothesis-based efficacy testing, the study aims to describe utilization, effectiveness, and safety patterns in a real-world clinical setting. The planned sample size of 10,000 participants was selected on the basis of the following considerations: (1) precision—a sample size of 10,000 with an anticipated dropout rate of approximately 20% yields an effective analysis population of ≥8,000 participants, providing a two-sided 95% confidence interval of approximately ±0.5% for the primary endpoint (percent change in LDL-C), assuming a standard deviation of 22%; (2) adverse event detection—this sample size provides ≥80% power to detect adverse events occurring at a true rate of ≥0.04% (approximately 1 in 2,500); (3) subgroup analyses—the planned sample size enables adequately powered descriptive analyses across pre-specified subgroups defined by cardiovascular risk category, prior lipid-lowering treatment history, dose (2/10 mg vs 4/10 mg), age, sex, and presence of diabetes; and (4) representativeness—a sample of this magnitude enrolled across multiple centers throughout Korea is expected to reasonably reflect the heterogeneity of the target population in routine clinical practice.

### Statistical analysis

2.6

#### Analysis populations

2.6.1

The full analysis set (FAS) includes all enrolled participants who received at least one dose of LivaloZet^®^ and have at least one post-baseline assessment. The per-protocol set (PPS) excludes participants with major protocol deviations. The safety analysis set (SAS) includes all participants who received at least one dose of LivaloZet^®^. The primary efficacy analysis will be performed on the FAS using last-observation-carried-forward (LOCF); the PPS will be analyzed as a sensitivity analysis.

#### Statistical methods

2.6.2

All hypothesis tests are performed at a significance level of 5%, and two-sided tests are used unless otherwise specified. SAS (Version 9.4 or higher, SAS Institute, Cary, NC, USA) is used as the software for statistical analysis. The significance level is not adjusted for per-visit analyses. Continuous variables are summarized using mean ± standard deviation (or median with interquartile range for skewed distributions). Categorical variables are summarized using counts and percentages. Two-sided 95% confidence intervals are reported alongside all point estimates for the primary and key secondary endpoints. Center-level variation will be evaluated using random-effects models with center as a random intercept, where appropriate. For variables with potentially non-normal distributions (notably triglycerides and high-sensitivity C-reactive protein), normality will be assessed graphically (histograms, Q–Q plots) and using the Shapiro–Wilk test prior to analysis; in cases of substantial skewness, results will be summarized as median (IQR) and analyzed using nonparametric methods (Wilcoxon signed-rank test for within-participant change, Mann–Whitney U test for between-group comparisons), with sensitivity analyses on log-transformed values reported as supportive evidence.

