#### Secondary endpoints

2.4.2

Percent change from baseline in LDL-C level at Week 48.Absolute change from baseline in LDL-C level at Week 24 and Week 48.Percent change and absolute change from baseline in lipid parameters at Week 24 and Week 48: Total cholesterol (TC), triglyceride (TG), HDL-C, non-HDL-C. Apolipoprotein B (Apo B) is not a required measurement; it will be collected and analyzed descriptively only when available from routine clinical practice.Achievement rate (%) for target LDL-C level at Week 24 and Week 48: Very high risk group <55 mg/dL, high risk group <70 mg/dL, diabetes group <100 mg/dL, moderate risk group <130 mg/dL, and low risk group <160 mg/dL according to the classification of cardiovascular disease risk groups.Medication adherence (proportion of days covered, PDC), persistence (time from initiation to discontinuation), dose modifications, and treatment switching during the 48-week observation period.

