#### Exploratory endpoints

2.4.4

Absolute change from baseline in blood glucose and glucose metabolism parameters at Week 24 and Week 48: Hemoglobin A1c (HbA1c), homeostasis model assessment of insulin resistance (HOMA-IR), homeostasis model assessment of β-cell function (HOMA-β).Percent change and absolute change from baseline in high sensitivity C-reactive protein (hs-CRP) at Week 24 and Week 48.

Exploratory laboratory parameters (HbA1c, HOMA-IR, HOMA-β, hs-CRP) are collected when available from routine clinical practice and are therefore subject to non-random missingness. To mitigate this limitation, baseline characteristics will be compared between participants with and without available measurements, and inverse-probability-of-availability weighting will be considered as a sensitivity analysis when interpreting these endpoints.

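### The signed-rank test planned for skewed TG and hs-CRP is not confined to absolute change; applied to percent change it leans toward a rise and can mask or reverse small true falls

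*Protocol article*

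**What the plan says.** Section 2.4.2 lists as secondary endpoints "Percent change and absolute change from baseline in lipid parameters at Week 24 and Week 48: Total cholesterol (TC), triglyceride (TG), HDL-C, non-HDL-C". Section 2.4.4 lists as exploratory "Percent change and absolute change from baseline in high sensitivity C-reactive protein (hs-CRP) at Week 24 and Week 48". Both variables therefore have a percent-change and an absolute-change endpoint.

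Section 2.6.2 names TG and hs-CRP as the variables most likely to be non-normal. If skewness is substantial, they are summarised by median and IQR and "analyzed using nonparametric methods (Wilcoxon signed-rank test for within-participant change, Mann–Whitney U test for between-group comparisons), with sensitivity analyses on log-transformed values"; the log-scale results count as supportive only. The same section sets the error rate: "All hypothesis tests are performed at a significance level of 5%, and two-sided tests are used unless otherwise specified". It does not say whether the change tested is percent, absolute or on the log scale.

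Section 2.5 calls the study descriptive and expects that the planned enrolment "yields an effective analysis population of ≥8,000 participants".

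**The concern.** The signed-rank test gets its null distribution by flipping signs about zero, so it is calibrated only if the analysed quantity is symmetric about zero when nothing has changed. If baseline and follow-up are exchangeable, the absolute difference and the log ratio are symmetric. Percent change is not: its median is zero, but rises are larger in size than the matching falls and collect the larger ranks. The cause is the division by baseline, not skewness of TG or hs-CRP as such.

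A larger sample does not cure this; it makes the wrong answer more certain. At stake are a significant rise reported when nothing changed, a small true fall reported as no change or as a rise, and percent-change and absolute-change tests that disagree on the same data.

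**Working it through.** **Inputs from the protocol.** Two-sided 5% (2.6.2). Analysis population 10,000 × (1 − 0.20) = 8,000 (2.5). The only precision figure is for LDL-C: 1.96 × 22/√8,000 = 0.48, which agrees with the stated ±0.5%. No figure is given for TG or hs-CRP.

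**Assumptions.** Log-normal values, with log(follow-up/baseline) ~ N(d, s²) and d = 0 for no change. The protocol gives no s. I use 0.20–0.50 for TG and 0.7–1.1 for hs-CRP. Because hs-CRP is optional, its sample size is unknown; 500 and 2,000 are shown. The first three steps assume no selection on baseline.

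**Step 1: expected drift under no change.** Let D be percent change and p₂ = P(D₁ + D₂ > 0) for two independent participants. The expected signed-rank z is about √(3n) × (p₂ − 0.5). For n = 8,000, √24,000 = 154.9:
- s = 0.2: p₂ = 0.5276, z ≈ 154.9 × 0.0276 = 4.3
- s = 0.3: p₂ = 0.5405, z ≈ 6.3
- s = 0.4: p₂ = 0.5524, z ≈ 8.1
- s = 0.5: p₂ = 0.5634, z ≈ 9.8

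For hs-CRP with s = 0.9, p₂ = 0.5988: z ≈ 3.8 at n = 500 and 7.7 at n = 2,000. A calibrated test would have expected z = 0.

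**Step 2: simulation under no change (exchangeable log-normal pairs).**
- TG, n = 8,000: significant rise on percent change in about 98–99% of runs at s = 0.20 and 100% at s = 0.3, 0.4 and 0.5.
- TG, s = 0.4, smaller samples: 97.5% (n = 2,000), 50% (n = 500), 24% (n = 200).
- hs-CRP, s = 0.9: 97% (n = 500), 100% (n = 2,000).
- The same test on absolute change or the log ratio: about 4–7% in total for s = 0.3–0.5 and 3.5–5% for s = 0.9. With 400 runs the standard error around 5% is √(0.05 × 0.95/400) = 1.1 points, so these agree with the nominal level.

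**Step 3: true falls.** The break-even fall, at which p₂ = 0.5 and the test sees nothing, is roughly s²/4 on the log scale. Solved exactly, it is 1.0%, 2.2%, 3.7% and 5.6% for s = 0.2, 0.3, 0.4 and 0.5, and 10.2%, 15.4% and 21.0% for s = 0.7, 0.9 and 1.1.

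TG, n = 8,000, s = 0.4, test on percent change:
- 2% fall: called a rise in 98% of runs
- 3% fall: called a rise in 36%, a fall in 0%
- 4% fall: detected in 8%
- 5% fall: detected in 80%
- 10% fall: detected in 100%

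The log-ratio test detects the 2% fall in 99% of runs and the others in 100%.

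hs-CRP, n = 2,000, s = 0.9, test on percent change:
- 10% fall: called a rise in 79%
- 15% fall: detected in 3%
- 20% fall: detected in 72%
- 30% fall: detected in 100%

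The log ratio detects all four in 100%.

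**Step 4: selection on raised TG.** Section 2.2.1 lets TG ≥200 mg/dL qualify as dyslipidemia and counts TG ≥150 mg/dL toward metabolic syndrome. Suppose a fraction of participants is selected on baseline TG ≥150, with no true change, n = 8,000 and s = 0.35. The percent-change test then declares a rise in 99% of runs with 10% selected, about 25–27% with 25% selected, and 0% with 50% selected, where it declares a fall in 100%. The log-ratio test declares a false fall in 73–100% across these settings.

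**The case against.** The strongest reply is that 2.6.2 does not fix the faulty combination. It speaks only of within-participant change, the usual input to this test is follow-up minus baseline, absolute change is a listed endpoint, and the test is valid there. Percent change might be given as median and IQR alone. This stands in part: a reader might infer that the plan expressly applies the test to percent change, and it does not. But percent change is an endpoint for both variables, nothing confines the test to the other scale, and no other within-participant test is offered for the skewed case.

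A reader might also infer that substantial skewness, the trigger for the test, is what breaks it. It is not: the test held its level on absolute change in equally skewed data. Nor is the fault peculiar to rank tests. A one-sample t-test on percent change does worse: at s = 0.35 and n = 8,000, a true 5% fall has expected mean 0.95 × exp(0.35²/2) − 1 = +1.0% and was called a significant rise in 67% of runs.

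Finally, the study is described as descriptive, the median would sit near zero under no change, and log analyses are already planned. These soften the matter. Yet 2.6.2 does set 5% tests, and it ranks the log analysis below the test it would contradict.

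**Conclusion.** The point holds as a gap in the stated rule: the signed-rank test should not be open to use on percent change in TG and hs-CRP. The direction of the scale fault does not depend on s; its size does, and s and the hs-CRP sample size are assumptions.

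Two stronger readings are not supported. The first is that the study will almost certainly report a false TG rise. That needs no selection on baseline, whereas the entry criteria admit people on raised TG, and regression to the mean can offset or reverse the rise. This does not validate the percent-change test. It also distorts the log-ratio and absolute-change tests, so moving to the log ratio corrects the scale fault only. The second is that real falls are hidden in general. Only falls near or below break-even are affected, and a 10% TG fall was detected in every run at s = 0.4.

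The primary LDL-C endpoint is not shown to be affected.

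**What to change.** In 2.6.2, state the scale of each test:
- Limit the signed-rank test to absolute change.
- For percent change in TG and hs-CRP, make the log ratio (log follow-up minus log baseline) the main analysis, by paired t-test or by signed-rank test on the log ratio. Back-transform the mean log ratio to a geometric mean percent change with 95% CI.
- Give median (IQR) percent change as description only, with no test on it. Do not substitute a t-test on raw percent change.
- When reporting, note that no within-participant test here separates a treatment effect from regression to the mean.

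The cost is a short edit to 2.6.2, carried into the analysis plan. No new data are needed, since the log analysis is already planned as supportive. The small downside is a less familiar summary that requires positive values.

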#### Subgroup analyses

2.6.3

Pre-specified subgroup analyses will be performed for the primary endpoint by: (1) cardiovascular risk category; (2) prior lipid-lowering treatment history (treatment-naïve vs inadequate response); (3) dose (2/10 mg vs 4/10 mg); (4) age (<65 vs ≥65 years); (5) sex; (6) presence of diabetes mellitus; and (7) baseline LDL-C (<130 vs ≥130 mg/dL). Subgroup analyses are descriptive; no formal interaction testing is planned.

#### Handling of missing data

2.6.4

In the event of missing data, missing values for efficacy endpoints are imputed using the last observation carried forward (LOCF) method. However, baseline values are not carried forward to replace post-baseline values. Safety analyses are conducted using observed cases (OC) without imputation of missing data. LOCF was selected as the primary approach for efficacy endpoints because it is a widely accepted, conservative, and easily interpretable method in regulatory and observational research, and because in a single-arm descriptive study without between-group comparison the bias introduced by LOCF is generally toward attenuation of within-participant change rather than spurious between-group differences. We acknowledge, however, that LOCF assumes that the last observed value is representative of the subsequent (missing) value, which may not hold for participants who discontinue treatment due to lack of efficacy or adverse events; the multiple sensitivity analyses described below (observed cases, multiple imputation, MMRM) are therefore essential to evaluate the robustness of the primary findings in this 48-week observational setting. To address the potential bias introduced by LOCF, two sensitivity analyses will be performed: (i) observed-cases analysis without imputation; and (ii) multiple imputation under the missing-at-random assumption (m=20 imputations, predictive mean matching). Mixed-effects models for repeated measures (MMRM) including all available longitudinal observations will be conducted as an additional sensitivity analysis, with no imputation required. The robustness of the primary conclusion will be assessed by comparing point estimates and confidence intervals across these analytical approaches.

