#### Primary endpoint

2.4.1

Percent change from baseline in LDL-C level at Week 24 (calculated, see Section 2.6.4 for LDL-C measurement method).

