#### Anticipated attrition and loss to follow-up

2.6.6

Based on prior Korean real-world observational studies of lipid-lowering therapy, the anticipated attrition rate at Week 24 is approximately 10–15%, and at Week 48 approximately 20–25%. Participants lost to follow-up will be retained in the FAS using LOCF for the primary analysis, with sensitivity analyses as described in Section 2.6.4. Reasons for discontinuation will be systematically captured (e.g., adverse event, lack of efficacy, patient withdrawal, switch to alternative therapy, loss to follow-up).

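### At Week 48 the plan's case for LOCF as conservative is unsupported: if leavers lose effect, LOCF overstates the LDL-C reduction, and no listed sensitivity analysis would show it

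*Protocol article*

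**What the plan says.** Under Handling of missing data (2.6.4), "missing values for efficacy endpoints are imputed using the last observation carried forward (LOCF) method", with one limit: "baseline values are not carried forward to replace post-baseline values". The choice is defended on the ground that "it is a widely accepted, conservative, and easily interpretable method in regulatory and observational research", and because in a single-arm study "the bias introduced by LOCF is generally toward attenuation of within-participant change rather than spurious between-group differences".

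The same section concedes that the last value may not represent later ones in people who stop because the drug fails or is not tolerated. It calls the sensitivity analyses essential for that reason. They are observed cases, "multiple imputation under the missing-at-random assumption", and MMRM; section 2.6.1 adds the per-protocol set. Robustness is to be judged by comparing estimates and intervals across these approaches.

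The primary endpoint (2.4.1) is "Percent change from baseline in LDL-C level at Week 24". The secondary endpoints (2.4.2) include "Percent change from baseline in LDL-C level at Week 48", the absolute change and the LDL-C target achievement rate. Table 1 schedules lipids at baseline, Week 24 and Week 48, with optional unscheduled values. Section 2.6.6 expects that "the anticipated attrition rate at Week 24 is approximately 10–15%, and at Week 48 approximately 20–25" percent.

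**The concern.** LOCF pulls an estimate toward no change when the carried value precedes the full effect. The bar on carrying baseline removes the most obvious way for that to happen here. What reaches Week 48 is normally a Week 24 value, taken after about half a year on study. If a participant then leaves and LDL-C drifts back up, the carried value is too low, and both the mean reduction and the target achievement rate look better than they are. That is the opposite of the direction the plan states.

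The second part is the safeguard. The plan admits that LOCF may fail after discontinuation and relies on three further analyses to reveal it. Observed cases leaves the missing people out. Multiple imputation under missing at random and MMRM predict them from people still observed who had similar earlier values. None lets a leaver lose effect because of leaving. A reader told that all approaches agree could take this as reassurance on a question that none of them examined.

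**Working it through.** **Inputs from the article.** N = 10,000, SD 22%, analysed n = 8,000 and a 95% interval of about ±0.5 for the primary endpoint (2.5). Attrition of 10–15% at Week 24 and 20–25% at Week 48 (2.6.6).

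**Assumptions, not in the article.** Dropout is monotone, with no later unscheduled lipid value. The mean on-treatment change is −20, −35 or −50%. Leavers lose none, half or all of it.

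**1. The plan's own figure.** 1.96 × 22 / √8000 = 0.482, which reproduces the stated ±0.5. With 9,000 or 8,500 participants having Week 24 data, the half-width is 0.455 or 0.468.

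**2. Share carried from Week 24 to Week 48.** Share = (a48 − a24) / (1 − a24), where a24 and a48 are the attrition rates.
- 10% then 20%: 0.10 / 0.90 = 11.1%
- 15% then 25%: 0.10 / 0.85 = 11.8%
- 15% then 20%: 0.05 / 0.85 = 5.9%
- 10% then 25%: 0.15 / 0.90 = 16.7%

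This is about 1,000 people in the first two cases, and 500 to 1,500 over the full range.

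**3. Overstatement of the mean Week 48 reduction.** Overstatement = share × size of on-treatment change × fraction of effect lost. At the 11.1% share, in percentage points:

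| On-treatment change | None lost | Half lost | All lost |
|---|---|---|---|
| −20% | 0 | 1.1 | 2.2 |
| −35% | 0 | 1.9 | 3.9 |
| −50% | 0 | 2.8 | 5.6 |

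For example, 0.111 × 35 × 0.5 = 1.9. At the 16.7% share, with −50% and all lost, it is 8.3. At the 5.9% share, with −20% and half lost, it is 0.6.

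**4. Rebound that matches the sampling error.** Half-width / share = 0.455 / 0.111 = 4.1 points of mean rebound among those carried forward. Over the attrition range this is 2.7 to 8.0 points.

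**5. Would the planned comparison show it?** A simulation used one million participants, two visits, mean −35 and SD 22 at each, an assumed correlation of 0.6 and 11.1% missing at Week 48. Regression imputation from Week 24 stood in for the missing-at-random methods. Mean percent change at Week 48:

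| Who leaves | Effect lost | Truth | LOCF | Observed cases | Missing at random |
|---|---|---|---|---|---|
| At random | none | −35.0 | −35.0 | −35.0 | −35.0 |
| At random | half | −33.0 | −35.0 | −35.0 | −35.0 |
| At random | all | −31.1 | −35.0 | −35.0 | −35.0 |
| Worse at Week 24 | none | −35.0 | −34.4 | −35.9 | −35.0 |
| Worse at Week 24 | all | −32.0 | −34.5 | −35.9 | −35.0 |

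With random dropout and loss of effect, all approaches agree and all are wrong. When worse responders leave and lose all effect, the sensitivity analyses lie further from the truth than LOCF. When they leave and keep their effect, LOCF is slightly conservative.

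**The case against.** A reader might infer that LOCF necessarily inflates the Week 48 result. The documents do not support that. They give no LDL-C after discontinuation, and a missing value is not the same as stopping the drug: section 2.6.6 lists loss to follow-up and a switch to other therapy among the reasons, and either may leave LDL-C treated. Dose increases are allowed at any time (2.1), so a missing value could have been lower. Someone who stops but attends Week 48 has an observed value. The carried value may also come from an unscheduled visit, or from a person already off drug at Week 24. These points stand and make the direction conditional.

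A reader might also say that all the analyses share one assumption. They do not. LOCF assumes constancy, observed cases needs missingness close to completely at random, and imputation and MMRM assume missing at random and can use a leaver's own Week 24 value. What they have in common is narrower: none models loss of effect after leaving.

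Nor does the point reach the primary result in any important way. With baseline barred, there is almost nothing to carry into Week 24. The ±0.5 is stated for that endpoint and serves only as a yardstick here. The 52–53% reduction cited in the Discussion comes from a randomised trial; this study also enrols inadequate responders to existing therapy, so the figure may not transfer, which is why a range is used.

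Finally, the article acknowledges that LOCF may fail and may not fully handle informative missingness, and an SAP, not shown, could hold a not-at-random analysis. But the acknowledgement does not correct the stated direction of bias, and the checks the article names for that failure cannot detect it.

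**Conclusion.** The point holds in conditional form. For Week 48 percent change, absolute change and target achievement, the description of LOCF as conservative and attenuating lacks support. If leavers lose effect, the mean reduction is overstated by about 1 to 3 points (half lost) or 2 to 6 points (all lost) at the 11.1% share. If the effect is kept there is no bias under random dropout; if LDL-C would have fallen further, or if poor responders leave without losing effect, LOCF attenuates. The sizes rest on the plan's attrition figures and on assumed on-treatment changes and losses of effect. For target achievement only the direction can be given. The planned robustness comparison cannot distinguish these cases. Because the effect falls on secondary endpoints of a single-arm descriptive study, this should be fixed but does not threaten the primary result.

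**What to change.** In section 2.6.4, delete the rationale that LOCF is conservative and biased toward attenuation, or state that at Week 48 it may overstate the effect if participants lose response after leaving.

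Add one not-at-random sensitivity analysis for Week 48. This could be delta-adjusted or tipping-point multiple imputation, or return-to-baseline imputation for participants recorded as stopping for adverse event, lack of efficacy or withdrawal, with switchers handled separately because their LDL-C may still be treated. If the SAP already has such an analysis, a sentence naming it in section 2.6.4 is enough.

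Making MMRM or multiple imputation the main analysis is not required and would not cure the problem by itself, as the last row of the simulation shows.

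The cost is a wording change and one extra analysis. Reasons for discontinuation, persistence and switching are already to be collected, so no new data are needed. The Week 48 result may look less favourable.
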